## Abstract

**Background:**

Cleft palate is among the most common birth abnormalities. The success of primary surgery in the early months of life is crucial for successful feeding, hearing, dental development, and facial growth. Over recent decades, age at palatal surgery in infancy has reduced. The Timing Of Primary Surgery for cleft palate (TOPS) trial aims to determine whether, in infants with cleft palate, it is better to perform primary surgery at age 6 or 12 months (corrected for gestational age).

**Methods/design:**

The TOPS trial is an international, two-arm, parallel group, randomised controlled trial. The primary outcome is insufficient velopharyngeal function at 5 years of age. Secondary outcomes, measured at 12 months, 3 years, and 5 years of age, include measures of speech development, safety of the procedure, hearing level, middle ear function, dentofacial development, and growth. The analysis approaches for primary and secondary outcomes are described here, as are the descriptive statistics which will be reported. The TOPS protocol has been published previously.

**Discussion:**

This paper provides details of the planned statistical analyses for the TOPS trial and will reduce the risk of outcome reporting bias and data-driven results.

**Trial registration:**

ClinicalTrials.gov NCT00993551. Registered on 9 October 2009.

**Supplementary Information:**

The online version contains supplementary material available at 10.1186/s13063-020-04886-y.

## Background

Clefts of the lip and/or palate are among the most common birth anomalies, occurring with an incidence of 1 in 600 births [1]. The timing of palatal surgery has been a controversial issue since the 1930s [2]. Traditionally, rationale for delaying hard palate surgery was partly based on the belief that postponing the trauma of palatal closure may reduce maxillary growth disturbance. However, there is little evidence that facial skeletal growth in individuals with isolated cleft palate is substantially affected by different surgical protocols, though maxillary arch form, especially transversely, may be affected [3–6].

Over recent decades, the age at which palatal surgery is carried out has reduced. This has led to one-stage palatal closure within 12 months of age at cleft units in Europe and the USA. Protagonists of early closure of the palatal cleft have proposed that since speech is a learnt behaviour, the sooner an intact anatomy is created, the better [7–10]. As yet, however, there is no evidence that early surgery would lead to better speech development.

The Timing of Primary Surgery for cleft palate (TOPS) trial is an international, two-arm, parallel group, randomised controlled trial designed to determine whether, in infants with isolated cleft palate, it is better to perform primary surgery at age 6 or 12 months (corrected for gestational age). This research will investigate the effect of the timing of surgery by assessing and comparing speech development outcomes measured across 12 months, 3 years, and 5 years of age. In addition, secondary outcomes include safety of the procedure, hearing level, middle ear function, dentofacial development, and growth. The protocol paper for the TOPS trial has been published previously [1]; the aim of this paper is to report in detail the statistical analysis plan. This paper has been prepared according to the published guidelines on the content of statistical analysis plans [11].

## Methods and design

### Trial design

TOPS is an international, multi-centre trial using a parallel arm design aiming to detect whether surgery at 6 months is superior to surgery at 12 months. Infants with a diagnosis of cleft palate are randomised to receive primary surgery for cleft palate using a standardised technique (the Sommerlad technique [12]) at either 6 months or 12 months (corrected for gestational age). Eligible patients are randomised on a 1:1 basis using minimisation routine, incorporating a random element to reduce predictability, to balance the two groups by surgeon (*n* = 24) and size of cleft (soft palate only vs. soft and hard palate). The nature of the intervention prevented this trial from being blind to participants or their carers. However, speech outcomes, at ages 12 months, 3 years, and 5 years, will be rated blind to the randomly allocated group by independent assessment of speech recordings taken at visit. The primary outcome is assessed at age 5 years with secondary outcomes assessed 48 h and 30 days post-surgery and at age 12 months, 3 years, and 5 years. Full details of the trial design, study population, and study procedures have been published previously [1].

The trial is registered with the ClinicalTrials.gov Identifier: NCT00993551 (registered: 9 October 2009).

### Objectives

The primary objective is to determine whether surgery for cleft palate, using the Sommerlad technique, at age 6 months when compared to surgery at age 12 months improves velopharyngeal function at age 5 years. Secondary research objectives include whether timing of surgery improves speech development, safety of the procedure, hearing level, middle ear function, dentofacial development, and growth.

### Outcomes

#### Primary outcome

The primary outcome is defined as a dichotomous outcome of whether the child has been perceived by Speech and Language Therapists (SLTs), following independent review of speech recordings, to have insufficient velopharyngeal function at age 5 years or not. Velopharyngeal insufficiency is measured by Velopharyngeal Composite Score (VPC) sum, which is a sum of scores, based on three components: hypernasality, non-oral errors, and velopharyngeal insufficiency (VPI) symptoms. Each component is classified and each classification mapped on to a score, see Table 1. The sum of the three scores, see Eq. 1, gives the VPC sum on the scale 0–6 [13]. Scores ≥ 4 on this scale will be considered insufficient.

**Table 1 Tab1:** Calculating the VPC sum

Component	Classification	Score for component
Hypernasality	Within normal limits	0
	Mild resonance	1
	Moderate/severe resonance	2
Non-oral errors	0–2 errors	0
	3–5 errors	1
	≥ 6 errors	2
Velopharyngeal insufficiency symptoms	0–2 symptoms	0
	3–5 symptoms	1
	≥ 6 symptoms	2

*Equation 1: Using the three component scores to calculate VPC sum*
1$$ \mathrm{VPC}\kern0.5em \mathrm{sum}=\kern0.5em \mathrm{Hypernasality}\kern0.5em \mathrm{score}+\mathrm{Active}\kern0.5em \mathrm{non}-\mathrm{oral}\kern0.5em \mathrm{errors}\kern0.5em \mathrm{score}+\mathrm{VPI}\kern0.5em \mathrm{symptoms}\kern0.5em \mathrm{score} $$

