#### Secondary outcomes

Secondary outcome measures are defined in the following list. Outcomes 1 to 5 are a measure of speech development, which are classified by SLTs following independent review of speech recordings. Outcomes 6, 7, 8, and 10 are a measure of safety of the procedure, hearing level, middle ear function, and growth respectively and are measured at the relevant follow-up visits. Outcome 9 is a measure of dentofacial development measured independently on a profile photograph and maxillary arch impression taken during the 5-year follow-up visit.
*Velopharyngeal function at age 5 years:*
a*Velopharyngeal composite score summary (VPC sum)*: a long ordinal outcome of individual score that contributes to the primary outcome, see Table 1. This score is measured on a scale of 0–6.b*Insufficient velopharyngeal function (VPC rate):* a dichotomous outcome of whether the child has “insufficient” VPC rate.*Velopharyngeal function at age 3 years:*
a*Insufficient velopharyngeal function (VPC rate):* a dichotomous outcome of whether the child has “insufficient” VPC rate.b*Velopharyngeal insufficiency symptoms:* a bounded continuous outcome, the proportion of times that a target consonant uttered has a velopharyngeal insufficiency symptom. Each child will attempt a minimum of 15 and a maximum of 30 predetermined target consonants (in words).*Canonical babbling at age 12 months:*
a*Canonical babbling present:* a dichotomous outcome of whether the child is “canonical” or “not canonical”.b*Canonical babbling ratio:* a bounded continuous outcome, the proportion of times that a syllable produced is “canonical”. Determined as the average proportion from the three SLTs undertaking independent review.c*Consonant inventory:* a continuous outcome of the number of unique consonants, identified by at least two of three SLTs undertaking independent review, uttered by a child.*Articulation at age 3 years:* Each child is required to have attempted a minimum of 15 and a maximum of 30 predetermined target consonants (in words) for articulation assessment.

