### Sample size

The sample size calculation was based on a test for proportions using a normal approximation: 292 participants per arm will allow a reduction in insufficient velopharyngeal function at 5 years from 40 to 29% to be detected with 80% power using a chi-squared test (2-sided significance test at 0.05 level). The estimate of 40% was obtained using data from a pilot trial of 50 5-year-old participants, conducted during the planning period for the grant application [18]. To allow an approximate attrition of 10%, 648 participants will be recruited. Restating the power for 300 participants per arm will allow the same difference to be detected with 81% power using a chi-squared test (2-sided significance test at 0.05 level). To consider the potential impact of variability around the value of 40%, 300 participants with valid data per group would provide 80% power to detect a reduction from 30 to 20% and 76% power to detect a reduction from 20 to 12%.

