#### Analysis of primary outcome

The number of participants at age 5 years who have the primary outcome of insufficient velopharyngeal function (VPC sum ≥ 4) or not (VPC sum < 4) will be summarised overall, for each randomised group and for each region (defined according to the location of the recruiting site: Brazil, Scandinavia, UK) by frequencies and percentages. The numbers of insufficient velopharyngeal function or not between the randomised groups will be compared using a chi-squared test, with the relative risk [20] and 95% confidence interval (95% CI) also reported.

In the circumstance that the expected insufficient VPC sum or not for each randomised group contains less than five participants, thereby raising concerns over the appropriateness of a chi-squared test, then Fisher’s exact test will be used.

For inclusion in the primary analysis set, a participant must have an eligible 5-year speech recording for SLT assessment. An eligible speech recording requires the child to have attempted at least 18 of the 36 pre-specified target words for assessment of non-oral and VPI symptom and 5 of the 9 pre-specified words for hypernasality. Participants who have speech recordings that do not meet the inclusion criteria, have a recording that could not be assessed (e.g. insufficient sound), or did not complete a speech recording will be excluded from the analysis.

A sensitivity analysis will be performed to check the robustness of the results to the inclusion/exclusion set for speech recordings such that assessments made on:
Non-oral and VPI symptom recordings with less than 18 target words attempted are included;+Hypernasality recordings with less than 5 target words attempted are included;Audio recordings, where video recording not possible, for non-oral and VPI symptom are excluded;Any recordings taken outside of the speech recording follow-up window (Table 5) are excluded.

A multilevel logistic regression model (for insufficient VPC sum) adjusting for operating surgeon, size of cleft at baseline (soft palate only vs. soft and hard palate), randomised group, and an intercept will be applied to check the robustness of the results to an unadjusted analysis approach [21–24].

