##### Long ordinal, bounded continuous, and continuous outcomes

Outcomes of this type, see Table 6, will be summarised overall and for each randomised group by means and SDs, or medians and IQRs if data are skewed. Minimum and maximum values will also be presented.

Means will be compared between the two randomised groups using a *t* test or by using a non-parametric equivalent. Testing for normality of data distributions will be based using a QQ plot by randomised group. Ninety-five percent confidence intervals will be presented around the effect measure.

No sensitivity analysis will be performed.

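### The full 0–6 VPC sum (secondary outcome 1a) needs one pre-specified adjusted ordinal model, not a t test or unnamed rank test chosen from a plot; the cut at 4 can stay as the primary outcome

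*SAP article*

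**What the plan says.** All references are to the SAP article.

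- **Primary outcome** builds the VPC sum from three components scored 0 to 2, giving a scale of 0–6, and then cuts it: "Scores ≥ 4 on this scale will be considered insufficient".
- **Analysis of primary outcome** tests the cut: "The numbers of insufficient velopharyngeal function or not between the randomised groups will be compared using a chi-squared test", with a relative risk and 95% CI. A multilevel logistic model with operating surgeon and size of cleft checks robustness. That model and the exploratory analysis that counts secondary surgery both keep a binary endpoint.
- **Secondary outcomes**, item 1a, is the uncut score: "a long ordinal outcome of individual score that contributes to the primary outcome". In Table 6 it is the only outcome classed as long ordinal.
- **Long ordinal, bounded continuous, and continuous outcomes** sets the analysis of 1a: "Means will be compared between the two randomised groups using a" t test or a non-parametric equivalent. Normality is judged from QQ plots by randomised group, a 95% CI is promised around the effect measure, and sensitivity analysis is ruled out.
- **Short ordinal outcomes** offers a proportional odds model as one possible fallback for the five-level hearing severity outcome.
- **Trial design** states that allocation is minimised on surgeon (24 surgeons) and size of cleft.

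**The concern.** The primary objective is whether earlier surgery improves velopharyngeal function at 5 years. A child who moves from 3 to 0, or from 6 to 4, does not change the primary result. Only 1a can show such movement, so its analysis should be fixed in advance and give an estimate that can be read beside the primary result. As written it does neither:

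1. **The choice of test is left open.** A score with seven values always gives a stepped QQ plot. The choice between a t test and a rank test therefore becomes a judgement made by eye on outcome data split by arm.
2. **The estimate is left open.** The heading measure is a mean, but a rank test does not compare means, and the article does not say what its confidence interval would surround.
3. **The minimisation factors are ignored.** The binary outcome has an adjusted counterpart; 1a has none. If surgeon or cleft size predicts the score, the unadjusted interval will tend to be wider than it need be.

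At stake is how the ordered score is read, above all when the binary result is close to the threshold. A model chosen at that stage would be the data-driven analysis that the article's Discussion says the plan is meant to prevent.

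**Working it through.** **1. The plan's own figure.** Inputs from Sample size: 40% against 29%, 80% power, "2-sided significance test at 0.05 level"; from Trial design, 1:1 allocation. With pooled variance and no continuity correction, n per arm = [1.96·√(2·0.345·0.655) + 0.8416·√(0.40·0.60 + 0.29·0.71)]² / 0.11² = (1.3176 + 0.5620)² / 0.0121 = 292. This agrees with the stated "292 participants per arm". Power is 80.0% at 292 and 81.1% at 300 per arm, also as stated.

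Trial status reports 558 recruited. That is 279 per arm with no loss (power 78.2%), or 558 × 0.9 / 2 ≈ 251 per arm with the plan's 10% attrition (73.8%).

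**2. What the full scale could add.** The article gives no distribution over 0–6, only the 40%, so the shape is an assumption and was varied. The design effect as an odds ratio is (0.29/0.71) / (0.40/0.60) = 0.613 (inverse 1.632). Simulated trials (40,000 per scenario) at 292 per arm, where the cut has 80%, gave:

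| Assumed pattern | Full-scale power | Gain over the cut |
|---|---|---|
| Spread-out scores, common odds ratio, rank test | 89–92% | 9–12 points |
| Same, t test | 88–92% | 8–12 points |
| Spread-out scores, probit shift, either test | 88–94% | 8–14 points |
| 50% of controls at 0, common odds ratio | 84–87% | 4–7 points |
| All 60% below the cut at 0, common odds ratio | 80–82% | 0–2 points |
| Both sides of the cut merely rescaled | 58–81% | mostly negative |
| Children move only from 4 or more to 3 | rank 18–32%, t test 11–48% | strongly negative |

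At about 251 per arm, with spread-out scores, the figures are 74% for the cut and 85–89% for the full scale.

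The plan's existing options for 1a already deliver this power where it exists. The tie-corrected rank test is, in addition, the score test of the unadjusted proportional-odds model. The case for that model is therefore a fixed choice and a readable estimate, not extra power.

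**3. What the unnamed effect measure means in practice.** Apply the odds ratio 0.613 to every cumulative split (40 to 29% at the cut) and vary only the control shape:

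- 60% at 0 and 40% at 4: means 0.40 × 4 = 1.60 and 0.29 × 4 = 1.16, difference 0.44.
- 60% at 0 and 40% at 6: means 2.40 and 1.74, difference 0.66.
- 15% at each of 0–3 and 13.3% at each of 4–6: the mean is the sum of P(score ≥ k) for k = 1 to 6. Control: 0.85 + 0.70 + 0.55 + 0.40 + 0.267 + 0.133 = 2.90. Treated: 0.776 + 0.588 + 0.428 + 0.290 + 0.182 + 0.086 = 2.35. Difference 0.55.

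One design effect thus maps to mean differences of 0.44 to 0.66, so a mean difference cannot be set directly against 40 to 29%.

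The rank branch can be worse. In the first shape both medians are 0. The treated child scores lower with probability 0.71 × 0.40 = 0.284, higher with 0.29 × 0.60 = 0.174, and ties with 0.542. The median pairwise difference (Hodges–Lehmann) is therefore also 0, although the arms truly differ. A small p value could stand beside an estimate of zero. The odds ratio is 0.613 in all three shapes.

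**The case against.** **The full score is already pre-specified.** This stands. Outcome 1a is listed first among the secondary outcomes, has a planned test and interval, and pays no multiplicity penalty because none is applied. The point is how it is analysed, not that it is absent.

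**The t test is serviceable at this size.** Largely true: with 250 or more per arm, a comparison of means does not need normal data. That is a reason to drop the QQ-plot rule, not to keep it. A t test fixed in advance would meet the first complaint but not the second or third.

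**Leaving 1a unadjusted matches the primary test.** True, but the primary test has an adjusted robustness model and 1a has none.

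**A reader might infer that the cut makes the primary analysis defective, or wastes 8–14 points of power.** The documents do not support this. Outcome definition, sample size ("from 40 to 29% to be detected with 80% power using a chi-squared test") and test agree with one another. The gain depends on a distribution the article does not give, shrinks with a heavy floor and reverses if benefit is confined to the threshold. Reasons for the cut may lie in the protocol or in the cited reference for the scale, neither of which is shown.

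**A promoted 1a could be used to rescue a missed primary result.** A fair warning; the plan should exclude this in words.

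**Conclusion.** The dichotomous primary outcome stands. The plan is weak in its rule for outcome 1a: the test is chosen by eye from data split by arm, the effect measure in the non-parametric branch is undefined, and there is no adjustment for the minimisation factors. These follow from the text and need no assumption.

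The power comparison is context. Full-scale analysis gains about 8–14 points if the shift is spread over the scale, about 0–7 if half or more of controls score 0 (common odds ratio), and loses if the effect is only at the cut. All of this assumes a control distribution that the article does not report. Changing the model for 1a does not raise the power of the primary test. The change is worth making because it is cheap and gives the ordered score an estimate on the same footing as the design effect.

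**What to change.** Before unblinding, amend the rule for long ordinal outcomes, a class that in Table 6 holds only 1a:

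- Replace the t test or rank test with a proportional-odds model in the primary analysis set, with terms for randomised group, size of cleft and surgeon. Treat surgeon as in the multilevel model already planned for the primary outcome, and state that treatment explicitly: with 24 surgeons and 558 children there are about 23 children per surgeon (558 / 24), spread over seven levels.
- Report the common odds ratio with its 95% CI, and the odds ratio at each cut from 1 or more to 6. The one at 4 or more is the primary dichotomy, so the link to the primary result is visible.
- Present it beside the primary result as supportive only, and state that it cannot turn a missed primary result into a positive conclusion.

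The cost is a short change of SAP wording and one model on data already collected. The primary outcome, its test and its alpha do not change. The downside is the proportional-odds assumption; the odds ratios by cut let the reader judge it and show whether any benefit is general or confined to the threshold.

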#### Secondary outcomes

Secondary outcome measures are defined in the following list. Outcomes 1 to 5 are a measure of speech development, which are classified by SLTs following independent review of speech recordings. Outcomes 6, 7, 8, and 10 are a measure of safety of the procedure, hearing level, middle ear function, and growth respectively and are measured at the relevant follow-up visits. Outcome 9 is a measure of dentofacial development measured independently on a profile photograph and maxillary arch impression taken during the 5-year follow-up visit.
*Velopharyngeal function at age 5 years:*
a*Velopharyngeal composite score summary (VPC sum)*: a long ordinal outcome of individual score that contributes to the primary outcome, see Table 1. This score is measured on a scale of 0–6.b*Insufficient velopharyngeal function (VPC rate):* a dichotomous outcome of whether the child has “insufficient” VPC rate.*Velopharyngeal function at age 3 years:*
a*Insufficient velopharyngeal function (VPC rate):* a dichotomous outcome of whether the child has “insufficient” VPC rate.b*Velopharyngeal insufficiency symptoms:* a bounded continuous outcome, the proportion of times that a target consonant uttered has a velopharyngeal insufficiency symptom. Each child will attempt a minimum of 15 and a maximum of 30 predetermined target consonants (in words).*Canonical babbling at age 12 months:*
a*Canonical babbling present:* a dichotomous outcome of whether the child is “canonical” or “not canonical”.b*Canonical babbling ratio:* a bounded continuous outcome, the proportion of times that a syllable produced is “canonical”. Determined as the average proportion from the three SLTs undertaking independent review.c*Consonant inventory:* a continuous outcome of the number of unique consonants, identified by at least two of three SLTs undertaking independent review, uttered by a child.*Articulation at age 3 years:* Each child is required to have attempted a minimum of 15 and a maximum of 30 predetermined target consonants (in words) for articulation assessment.
a*Percent consonants correct (PCC):* a bounded continuous outcome, the proportion of times that a target consonant is uttered correct.b*Percent correct placement (PCP):* a bounded continuous outcome, the proportion of times that a target consonant has the correct place of articulation.c*Percent correct manner (PCM):* a bounded continuous outcome, the proportion of times that a target consonant has the correct manner of articulation.d*Non-oral consonant errors:* a bounded continuous outcome, the proportion of times that a target consonant is realised as a non-oral error.e*Oral consonant errors:* a bounded continuous outcome, the proportion of times that a target consonant is realised as an oral error.*Articulation at age 5 years:* Each child is required to have attempted a minimum of 18 and a maximum of 36 predetermined target consonants (in words).
a*PCC:* a bounded continuous outcome, the proportion of times that a target consonant is uttered correct.b*PCP:* a bounded continuous outcome, the proportion of times that a target consonant has the correct place of articulation.c*PCM:* a bounded continuous outcome, the proportion of times that a target consonant has the correct manner of articulation.d*Non-oral consonant errors:* a bounded continuous outcome, the proportion of times that a target consonant is realised as a non-oral error.e*Oral consonant errors:* a bounded continuous outcome, the proportion of times that a target consonant is realised as an oral error.*Postoperative/long-term complications:*
a*Dehiscence:* a dichotomous outcome of whether the child has a postoperative dehiscence, measured 48 h and 30 days postoperatively.b*Infection:* a dichotomous outcome of whether the child has a postoperative infection, measured 48 h and 30 days postoperatively.c*Evidence of fistula:* a dichotomous outcome of whether the child has a postoperative fistula, assessed as “Yes” or “Probably”, measured 30 days postoperatively and at 3 and 5 years of age*.**Hearing level:*
a*At 12 months:*
i*Abnormal Transient Otoacoustic Emission (TEOAE):* a dichotomous outcome of whether the child has abnormal TEOAE.j*Abnormal sound field audiometry:* a dichotomous outcome of whether the child has abnormal sound field audiometry. Abnormal sound field audiometry is indicated by a measurement of > 30 dB HL for at least one of four frequencies tested: 500 Hz, 1000 Hz, 2000 Hz, or 4000 Hz.b*At 3 and 5 years:*
i*Abnormal pure tone audiometry in at least one ear:* a dichotomous outcome of whether the child has abnormal pure tone audiometry. If testing by pure tone audiometry is not possible, sound field audiometry can be used in its place. Abnormal audiometry in at least one ear is indicated by a measurement of > 20 dB HL using the pure tone method, > 25 dB HL for sound field, for at least one of four frequencies tested: 500 Hz, 1000 Hz, 2000 Hz, or 4000 Hz.j*Abnormal pure tone audiometry in both ears:* a dichotomous outcome defined in the same way as secondary outcome 7bi, for patients who have both ears tested and both tested ears indicate abnormal audiometry.k*Severity of better ear:* a short ordinal outcome of the severity of the better ear. If testing by pure tone audiometry is not possible, sound field audiometry can be used in its place. Each patient will be classified according to the average score in the better ear if pure tone, or both ears if sound field, across the four frequencies (500 Hz, 1000 Hz, 2000 Hz, or 4000 Hz) to the categories in Table 2 [14].*Middle ear function:*
a*Flat line tympanogram in at least one ear:* a dichotomous outcome of whether the child has flat line tympanogram, assessed at age 12 months, 3 years, and 5 years. Children with either ear measured as “Type B” will be classified as having flat line tympanogram in at least one ear.b*Flat line tympanogram in both ears:* a dichotomous outcome of whether the child has flat line tympanogram, assessed at age 12 months, 3 years, and 5 years. Children with both ears measured as “Type B” will be classified as having flat line tympanogram in both ears.*Dentofacial development at age 5 years:*
a*Soft tissue ANB angle:* a continuous outcome of the angle between soft tissue nasion (points A and B) measured using a profile photograph [15].b*Maxillary arch constriction score:* a bounded continuous outcome, measured using the Huddart/Bodenham scoring system, on a maxilliary and mandibular arch impression. A score can range from − 24 to 8 and is measured in whole numbers [16, 17]*.**Growth at 12 months:*
a*Nude weight:* a continuous outcome, measured in grammes and recorded to the nearest whole number.b*Crown to heel length:* a continuous outcome, measured in centimetres and recorded to one decimal place.c*Occipitofrontal circumference:* a continuous outcome, measured in centimetres and recorded to one decimal place.

**Table 2 Tab2:** Classifying severity in better ear

Average dB HL	Severity
≤ 20 dB HL	Normal
Between 21 and 40 dB HL	Mild
Between 41 and 70 dB HL	Moderate
Between 71 and 95 dB HL	Severe
> 95 dB HL	Profound

